## Abstract

**Background:**

A SARS-CoV-2 infection can lead from asymptomatic through to critical disease in a dynamic and unpredictable course within a few days. The challenge in outpatient monitoring the highly contagious COVID-19 disease during the ongoing pandemic is to filter severe courses followed by admission to hospital with the aim of preventing an overburdening of clinics. However, little is known of the effect of risk factors on the course of the infection of outpatient patients. To support general practices in managing high risk patients, we designed a COVID-19 surveillance and care tool (CovidCare). It includes an initial assessment of yet known risk factors and symptoms and a continuous telephone monitoring of signs and symptoms. This study aims to investigate the effects of different risk factors on the course of the COVID-19 disease, utilisation of different health care services and to gain insights into the utilisation of CovidCare in general practices.

**Methods:**

We will conduct a multi-centered prospective, longitudinal non-controlled observational trial of COVID-19 patients in general practices. Overall, 700 GPs who participate in general-practice centered care by the AOK Baden-Württemberg (large German sickness fund) are eligible and will be invited for study participation, including adult, outpatient COVID-19 patients (or urgent suspicion and ≥ 50 years) with at least one additional known risk factor, who participate in general-practice centered care. The primary outcome is hospitalisation due to COVID-19. Secondary outcomes are diagnosis of pneumonia, utilisation of palliative care, mortality rate, anxiety and identification of predictive risk factors. Quantitative data analysis will focus on valid descriptive figures and mixed regression models. The accompanying process evaluation is based on interviews and questionnaires from general practice staff and patients. The analysis of the process evaluation is descriptive and explorative.

**Discussion:**

The use of the COVID-19 surveillance and care tool is expected to encourage the provision of structured quality of care during the ongoing pandemic. This trial will provide an understanding of the COVID-19-disease and the effect of several risk factors on the course of the disease and health care utilisation. The results can be used for a better management of the COVID-19 pandemic and its consequences.

**Trial registration:**

German Clinical Trials Register DRKS00022054.

**Supplementary Information:**

The online version contains supplementary material available at 10.1186/s12875-021-01515-8.

## Background

Since late December 2019, the newly emerged virus SARS-CoV-2 spreads across the globe, causing the COVID-19 disease. Having started in Wuhan, China, SARS-CoV-2 has spread rapidly, causing catastrophic states for health systems, economies and politics. SARS-CoV-2 causes respiratory symptoms such as coughing, a sore throat, and fever, and can lead to mild, severe and critical disease in a dynamic course over a few days. Several risks associated with a worse course have been identified, such as age (50 years and older), comorbidities (such as diabetes, cardiovascular disease, pulmonary disease), oncological diseases, immunodeficiency, obesity or nicotine consumption. However, also young patients without risks sometimes show a severe to critical course [1, 2]. Patients with severe symptoms are treated in hospitals, often in intensive care units. However, for the majority of patients hospitalisation is not indicated [3, 4] and they remain in their home in a status of officially ordered quarantine. The responsible care provider for these patients remains their general practitioner (GP). In order to prevent healthcare systems to be overwhelmed, patients with mild diseases should be treated by outpatient care providers and more severe courses need to be detected at an early stage and responded to appropriately in a timely manner. However, little is known of the effect of the risk factors identified on the course of the disease. There is a wide range of various models for diagnosing COVID-19, predicting the prognosis of patients with COVID-19 or being admitted to hospital for COVID-19 [5, 6] as well as models to support risk stratification scores [7]. In Germany, the indication of a hospital admission is decided by the outpatient doctor dependent upon age, comorbidities, breathing rate and oxygen saturation [8]. Guidelines on using drugs for the treatment of COVID-19 have also been published and are continuously updated, but are still limited to symptomatic and risk adapted anticoagulation in the outpatient setting [9]. However, it requires a comprehensive approach for the detection and treatment of COVID-19 symptoms. Moreover, in order to keep infection risks in general practices to a minimum, a change of the traditional consultation is necessary. Telemedicine based approaches such as remote monitoring has shown to be effective as in-person care [10, 11]. Therefore, in the presented study data from a COVID-19 surveillance and care tool, that is used in general practices to support outpatient care for patients with increased risk, including structured telephone assessment and monitoring, are analyzed in order to gain a more comprehensive understanding of the COVID-19 disease.

### Objectives

The overall aim of the study is to gain insights into the effects of different risk factors on the course of the COVID-19 disease and the utilisation of different health care services. The accompanying process evaluation aims at gaining insights into the utilisation of the surveillance and care tool in general practices.

## Methods/design

### Trial and study setting

This is a multi-center prospective longitudinal non-controlled observational study of COVID-19 patients exploring the effect of different risk factors on disease progression. The process evaluation follows an exploratory sequential mixed-methods design, qualitative data from interviews and quantitative data from questionnaires and the CovidCare-module. After all qualitative data have been collected, analysed and important aspects have been identified, questionnaires will then be developed based on the qualitative findings to further enrich the results. The interview guides and questionnaires have not been published previously.

### Eligibility criteria {10} and informed consent

All GPs who participate in general-practice centred care (GP-centred care) by the AOK Baden-Württemberg care are eligible for using the CovidCare-module within the CareCockpit software. The eligible practices are informed by the GP-centred care contract partners about the possibility to use CovidCare for the care of confirmed and suspected COVID-19 patients.

Prerequisites are the online registration and participation in an online training including exam questions for the handling of the software. After the successful completion of the exam, general practices can download the software.

All general practices who have successfully completed the exam and who download the software are automatically provided with an invitation for participation in the CovidCare study as well as an information leaflet and a participation form.

General practices can participate in the CovidCare study by sending the signed participation form to the study central office (Department of General Practice and Health Services Research, University Hospital Heidelberg).

Additional time expenditure for GP-practices for participation in the study concern information of eligible patients, obtaining the informed consent as well as the weekly data transfer. Time expenditure for this study depends on the number of patients a general practice can include in the study.

The study population comprises of COVID-19 patients treated in general practices who meet the inclusion criteria. The study population for the process evaluation consists of GPs, VERAHs (Care Assistant in General Practice (*Ver*sorgungs*a*ssistentin in der *H*ausarztpraxis)) and patients participating in the CovidCare study.

The following groups of patients are eligible for participating in the study:

COVID-19 patients aged 18 or older (as per definition patients with symptoms of an infection of any severity and positive test for SARS-CoV-2), who are in domestic isolation* and who have at least one risk factor**

OR

2.Patients aged 50 and older with a clinically urgent suspicion of COVID-19 (such as acute respiratory symptoms of any severity), without verification of SARS-CoV-2 and who have at least one risk factor**/***

*Domestic isolation: includes persons for whom the authorities highly recommend further social distancing beyond the restrictions as currently ordered.

*** This criterium might by subject to potential changes and might be further adapted according to (a) the current epidemiological situation, (b) the requirements of the Robert-Koch-Institute (RKI), (c) the test strategy as well as (d) the test capacity.

**Risk factors following the definition by the RKI, with own additions:
Diabetes mellitus (Types I and II)Cardiovascular disease (arterial hypertension, coronary heart disease, heart failure, other such as atrial fibrillation, peripheral artery disease, condition after apoplexy)Pulmonary disease (COPD, bronchial asthma, other)chronical nephrological diseasechronical hepatic disease such as liver cirrhosisimmunodeficiency due to underlying disease (malignant primary hematological disease (e.g. leukemia/ lymphoma), leukocytopenia, condition after organ or stem cell transplantation or potentially immunosuppressive medication intake such as glucocorticoids, immunosuppressive drugs, immunomodulators, cytostaticsactive oncological disease with immunodeficiency (excluding for example localized skin cancer such as squamous cell carcinoma or basal cell carcinoma)obesity (body mass index > 35)active smokingDown syndrome

All patients have to be 18 years and older, insured with the AOK Baden-Württemberg, participate in GP-based care, and have written and spoken German language skills.

If patients are unable to give their informed consent into study participation, a legal representative of the patient has to give their informed consent for study participation of the patient.

Participants for the process evaluation have to participate in the CovidCare study as either patient or health care provider, are 18 years and older, have written and spoken German language skills and have to be able to give their informed consent.

No further exclusion criteria have been defined.

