### Outcomes

The primary outcome is hospitalisation due to COVID-19. The following indicators have been identified as secondary outcomes:

Diagnosis of pneumonia in confirmed and suspected COVID-19 patients [14].Utilisation of palliative care by confirmed and suspected COVID-19 patients during quarantine or stay at hospital.Mortality rate of confirmed and suspected COVID-19 patients (death at home, death in hospital, death in long-term care institution).Anxiety in confirmed and suspected COVID-19 patients using the Generalized Anxiety Disorder Index (GAD-2) [15].Identification of predictive risk factors for the outcomes such as hospitalisation, intensive care and mortality.

For the process evaluation we chose an exploratory sequential design. The process evaluation consists of a qualitative strand and a quantitative strand.

Overall, for the process evaluation we use the RE-AIM framework according to Glasgow and colleagues [16] to assess reach, efficacy, adoption, implementation and maintenance of the CovidCare surveillance and care tool. Table 1 provides an overview of the outcomes, indicators and methods/instruments of the process evaluation according to the RE-AIM framework.

**Table 1 Tab1:** Concept of the process evaluation

Outcomes	Indicators (examples)	Methods/Instruments
1) Reach The extent to which patients are reached by the implementation of CovidCare as well as the number of patients who are willing or refused to participate in CovidCare.	• How have patients been approached • Number of patients approached • Number of patients willing to participate in CovidCare • Patients: Reasons for refusal and drop-out, exclusion rate • Number of contacts per patient (i.e. telephone monitoring, particularly in the critical phase as defined by the RKI as a proxy whether GPs treat their patients according to guidelines) • Characteristics of participating patients	S, I, DB
2) Efficacy The efficacy of the CovidCare-module includes positive and negative impacts/effects for patients and HCP as well as the patients’ quality of life and the patients and the HCP’s satisfaction with the intervention.	• Positive and negative effects on patients’ quality of life, perception of (quality of) care, disease coping • Effects on health care personnel in managing Covid-19 patients • Satisfaction of HCP and patients with CovidCare • Comparison with patients with Covid-19/suspected cases but WITHOUT additional risk factors or aged >50	S, I, DB

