### Statistical methods

#### Statistical methods for primary and secondary outcomes

Data analysis is explorative. Date of the full study population (general practices and patients) will be included in data analysis.

Descriptive statistics of all collected data will be performed. Continuous variables will be described using means, standard deviations, median, minimum, maximum, and first and third quartile. Categorical variables will be reported using absolute and relative frequencies.

The potential effect of sociodemographic characteristics (age, gender, living situation), risk factors (as described above) on the severity of the disease, utilisation of different care services (hospitalisation, intensive care unit, invasive ventilation, palliative care) will be estimated by models taking the clustered structure into account. Therefore, e.g. SAS PROC MIXED, PROC GENMOD or PROC GLIMMIX can be accordingly parametrized to determine fixed and random effects. In order to determine potential differences concerning mortality between particular strata there are also a couple of methods available to take a clustered structure into account. One option is a likelihood-based random effects (frailty) model. The baseline hazard could be either a priori determined (e.g., Weibull) or approximated by piecewise constant counterpart. The estimation could be carried out by adaptive Gaussian quadrature method which is implemented in SAS PROC NLMIXED.

Incubation, begin of the disease, and progression of the disease will be analysed descriptively.

Data analysis for the process evaluation is descriptive and explorative. Qualitative data from interviews will be transcribed according to established standards and will be analyzed with regard to the research questions with qualitative content analysis [17] or framework analysis using the software MAXQDA. Quantitative survey data and the indicators for the intervention fidelity will be analyzed descriptively.

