#### Methods for additional analyses (e.g. subgroup analyses)

Descriptive subgroup analyses are planned, especially in terms of patients’ age, gender, and risk factors. Adjustment of inference will be performed by multivariable regression analyses as described above.

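### Unverified suspected cases enter only from age 50 and are analysed with confirmed cases, so the age effect on COVID-19 hospitalisation is pulled toward the null by an unknown amount

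*Protocol article*

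**What the plan says.** Under Eligibility criteria, the protocol article opens two routes into the cohort, both requiring at least one risk factor. The first takes "COVID-19 patients aged 18 or older (as per definition patients with symptoms of an infection of any severity and positive test for SARS-CoV-2". The second takes "Patients aged 50 and older with a clinically urgent suspicion of COVID-19 (such as acute respiratory symptoms of any severity), without verification of SARS-CoV-2". A footnote to the second route says: "This criterium might by subject to potential changes and might be further adapted". The grounds it lists for a change include "c) the test strategy as well as (d) the test capacity".

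Statistical methods for primary and secondary outcomes fixes the analysis population: "Date of the full study population (general practices and patients) will be included in data analysis". It then names the predictors: "The potential effect of sociodemographic characteristics (age, gender, living situation), risk factors (as described above) on the severity of the disease". SARS-CoV-2 status is not in that list. Methods for additional analyses says "Descriptive subgroup analyses are planned, especially in terms of" age, gender and risk factors, and refers adjustment back to the same regression models.

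Under Outcomes, the primary outcome is hospitalisation due to COVID-19. Four secondary outcomes (pneumonia, palliative care, mortality, anxiety) name both groups of patients, for example "Mortality rate of confirmed and suspected COVID-19 patients".

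The Intervention description records SARS-CoV-2 status at the initial assessment and has the GP set a presumed onset date. The stated aim under Objectives is the effect of risk factors on the course of COVID-19.

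**The concern.** Age plays two parts here. It is one of the predictors whose effect the study wants to estimate, and it also decides whether a patient without proven infection can enter at all. Under 50 the share of patients without COVID-19 is zero, apart from false-positive tests. From 50 upward it is whatever fraction of the suspected patients had some other respiratory illness. Diagnostic certainty is therefore tied to age by design, and a model with age but no status term attributes the difference to age.

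For the primary outcome the direction can be reasoned out. A patient without COVID-19 cannot truly be hospitalised because of it, so such patients add mainly non-events, and only to the older group. The age effect shrinks. If the second entry route is widened or narrowed during the roughly 20 months of recruitment (30 April 2020 to 31 December 2021), the pooled estimate can also move with no change in the disease.

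At stake is the study's central result: a clinically important risk factor could look weaker than it is in patients who have COVID-19.

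**Working it through.** The protocol states no sample size, event rate, suspected share or proportion of suspected patients who truly have COVID-19. There is no figure of the plan's own to reproduce, and every risk below is an assumption chosen to show direction and scale.

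**Age effect.** Let f be the share of the 50-and-over group without COVID-19, that is, the suspected share times the non-COVID fraction among suspected patients. Let r be the risk of a recorded event in those patients. Assume a risk of 15% in patients of 50 and over with COVID-19 (the same whether confirmed or suspected) and 5% under 50.

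- Pooled risk at 50 and over: p = (1 − f) × 0.15 + f × r
- Odds ratio (OR): [p / (1 − p)] / [0.05 / 0.95]
- True OR: (0.15 / 0.85) / (0.05 / 0.95) = 3.35

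| Suspected share × non-COVID fraction | f | r | p | OR |
|---|---|---|---|---|
| 20% × 30% | 0.06 | 3% | 0.94 × 0.15 + 0.06 × 0.03 = 0.1428 | 3.17 |
| 40% × 50% | 0.20 | 3% | 0.80 × 0.15 + 0.20 × 0.03 = 0.1260 | 2.74 |
| 40% × 50% | 0.20 | 0% | 0.80 × 0.15 = 0.1200 | 2.59 |
| 60% × 80% | 0.48 | 3% | 0.52 × 0.15 + 0.48 × 0.03 = 0.0924 | 1.93 |
| 40% × 50% | 0.20 | 15% | 0.1500 | 3.35 |
| 40% × 50% | 0.20 | 20% | 0.80 × 0.15 + 0.20 × 0.20 = 0.1600 | 3.62 |

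The zero-risk row is what a correctly attributed primary outcome would give. The last two rows show what could happen with an outcome not tied to COVID-19: no bias when both illnesses carry the same risk, and bias away from the null when the other illness carries the higher one.

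**Shift with test policy.** Hold the non-COVID fraction at 50% and r at 3%. If the suspected share falls from 40% (f = 0.20) to 12% (f = 0.06), the OR rises from 2.74 to 3.17 while the disease is unchanged.

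**Comorbidity effect.** Logistic models were fitted to expected counts with age and one age-linked comorbidity. The assumptions were: 40% of the cohort under 50; comorbidity prevalence 30% under 50 and 60% from 50; baseline risk 3%; true ORs 3.0 for age and 2.0 for the comorbidity; 40% of the older group suspected, of whom 20% truly have COVID-19.

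| r | Pooled, no status: age / comorbidity | With status term: age / comorbidity | Confirmed only: age / comorbidity |
|---|---|---|---|
| 0% | 1.95 / 1.96 | 3.00 / 1.99 | 3.00 / 2.00 |
| 4% | 2.32 / 1.83 | 3.07 / 1.85 | 3.00 / 2.00 |
| 12% | 3.08 / 1.67 | 3.15 / 1.67 | 3.00 / 2.00 |

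At r = 0 the pooled comorbidity OR falls to 1.62 if patients with the comorbidity are more often enrolled as suspected (50% against 30%), and rises to 2.35 if the pattern is reversed. Two things follow. The direction for comorbidities is uncertain. A status term largely repairs the age effect, but it leaves the comorbidity effect almost where it was when non-COVID patients have events.

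**The case against.** The strongest reply is that the exact covariates and analysis sets belong to a statistical analysis plan that is not shown. The article calls the analysis explorative, names its procedures as examples and introduces its subgroups as a non-exhaustive list. Status is recorded, so an unseen plan could adjust or stratify. This stands as a caution: a reader should not infer that status will never be used. It does not remove the point. The article itself fixes the pooled population and the age-dependent entry rule, and a later plan cannot undo the entry rule. Being explorative does not correct a systematic bias in the stated aim.

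Other parts of the reply hold, and they limit what can be claimed:

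- A reader might infer that comorbidity effects are diluted in the same way as age. With age in the model and no non-COVID events, the loss is almost nil (2.00 to 1.96), and the bias can reverse.
- A reader might infer that every outcome is defined on both groups together. That wording is attached to four secondary outcomes, not to the primary one, and it says who is assessed rather than that one pooled estimate will be reported.
- A reader might infer that the primary outcome cannot be established in a patient who entered unconfirmed. The article does not say how attribution is made, and the module's timelines include a positive test result, so later confirmation is possible.
- A reader might infer that the suspected share did move. The footnote says only that the criterion might change, and discloses this openly.

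**Conclusion.** The point holds for the age effect. As written, the plan ties diagnostic certainty to age and pools across it, so the age effect on hospitalisation due to COVID-19 is pulled toward the null. This requires only that some suspected patients do not have COVID-19 and that their risk of a recorded event is below that of COVID-19 patients of the same age. That risk is zero if attribution is correct.

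For mortality and pneumonia the bias may go either way. Effects of age-linked comorbidities may also be affected, in an uncertain direction.

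The size is unknown. The illustrated movement from 3.35 to 2.74 (2.59 at zero non-COVID risk), and the span of about 3.2 to 1.9, rest wholly on assumed risks and shares. An OR below 1.9 within these non-COVID shares needs a non-COVID risk under the 3% used for the span. A shift over the recruitment period is a possibility that the protocol allows, not an event it reports. The change should be made, because the analysis as stated does not match the stated aim.

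**What to change.** - Run the main risk-factor models in patients test-confirmed at entry (the first eligibility route), using the status recorded at the initial assessment.
- Report patients who entered as suspected separately.
- Keep the pooled set as a sensitivity analysis, with entry status and its interaction with the risk factors among those aged 50 and over. A status main effect alone is not enough for the comorbidities.
- Add calendar period of onset as a covariate, and record the date of any change to the suspected-case criterion.
- Do not define the main set by test status at closing. No such field is listed for the closing contact, and later testing can depend on the outcome: a suspected patient who is admitted may be tested and move into the set while a mild case stays out. That route exists only from age 50 and would bring in a new age-linked bias.

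Entry status and onset date are already collected, so the change is one of wording. The price is a smaller main analysis set, whose results apply to patients with a positive test at entry.
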